## Abstract

Chronic heart failure (CHF) is a common cardiovascular disease with high mortality and a poor prognosis, which places heavy burdens upon society and families. Traditional Chinese medicine (TCM) has been used extensively as complementary treatment for CHF. *Guanxinshutong* (GXST) capsules are used commonly for the treatment of coronary heart disease (CHD). Experimental research and small-sample clinical trials have shown that GXST can attenuate CHF. However, the effects of GXST as complementary medicine in CHF treatment lack high-quality clinical evidence. We have designed a multicenter, randomized, double-blind, placebo-controlled clinical trial that explores the efficacy and safety of using GXST compared with placebo for patients with CHF with reduced left ventricular ejection fraction (LVEF). A total of 480 participants will be assigned randomly to the GXST group or placebo group at a 2:1 ratio. GXST and placebo will be added to standard treatment for 12 weeks, and then followed up for another 40 weeks. The primary outcome is the improvement value of 6-min walk distance, and the secondary outcomes include plasma levels of N-terminal pro-B-type natriuretic peptide, New York Heart Association classification, Minnesota Living with Heart Failure Questionnaire scores, echocardiographic parameters, and clinical endpoint events. Adverse events will be monitored throughout the trial. Data will be analyzed following a predefined statistical analysis plan. This study will show the effects of the specific use of GXST in CHF patients with reduced LVEF. The Research Ethics Committee of the Second Affiliated Hospital of Zhejiang Chinese Medical University has approved this study (2019-Y-003-02). Written informed consent of patients will be required. This trial is registered in the Chinese Clinical Trial Registry (ChiCTR1900023877). Our results will be disseminated to the public through peer-reviewed journals, academic conferences, and the Internet.

## Introduction

Chronic heart failure (CHF) is a complex clinical syndrome characterized by reduced cardiac output, insufficient organ perfusion, and venous congestion due to cardiac dysfunction (Coronel et al., 2001; Tan et al., 2010). CHF affects about 26 million people worldwide, with more than one million people hospitalized in the USA and Europe each year (Ambrosy et al., 2014). In China, it is estimated that 4.5 million aged 35–74 years suffer from CHF, and, with an increasingly aging population, the incidence of common cardiovascular diseases, such as hypertension, coronary heart disease (CHD), and CHF, continues to rise (Guo et al., 2003; Huo et al., 2019). CHF brings a heavy economic burden to society, families, and individuals, so new therapies and prevention strategies are needed.

According to guidelines for the diagnosis and treatment of heart failure set by the Chinese government in 2018, angiotensin-converting enzyme inhibitors (ACEIs), β-receptor blockers, and aldosterone receptor antagonists are recommended as “the golden triangle treatment” for patients suffering from CHF with reduced ejection fraction (Heart Failure Group of Chinese Society of Cardiology and Editorial Board of Chinese Journal of Cardiology, 2018). Although the use of the golden triangle treatment has improved the curative effect, this treatment plan is associated with hyperkalemia, deterioration of renal function (Heart Failure Group of Chinese Society of Cardiology and Editorial Board of Chinese Journal of Cardiology, 2018), limited improvement of symptoms, and unsatisfactory improvement in long-term survival (Pitt et al., 2014; Maisel et al., 2018). In recent years, the use of angiotensin receptor neprilysin inhibitors (ARNIs) has been considered as a therapeutic strategy in heart failure (McMurray et al., 2014). The PARADIGM-HF trial provided evidence that combined inhibition of the angiotensin receptor and neprilysin is superior to inhibition of the renin–angiotensin system alone in patients with CHF (McMurray et al., 2014). However, the ARNIs (tablets of sacubitril valsartan sodium) are not widely used in China currently.

Traditional Chinese medicine (TCM) is a popular type of supplementary and complementary medicine. TCM formulations have been employed widely and successfully for CHF treatment in China for more than 2000 years. Currently, the integration of Chinese and Western medicine has shown promising benefits in controlling symptoms, reducing mortality, improving cardiac function, and promoting quality of life in patients with CHF (Xu and Xu, 2011). In TCM, all the related symptoms, signs, tongue appearances, and pulse feelings at a certain stage of disease are summarized as a syndrome (“*Zheng*” in TCM) (Jiang et al., 2012). The syndrome is not only the core of TCM theory but also the base of the definitive diagnosis and efficacious therapies (Xu and Chen, 2008). According to Cui and colleagues, the basic syndrome type of CHF is “blood stasis syndrome” (Cui et al., 2009). The symptoms of CHF with blood stasis syndrome are palpitation, pain in the chest and hypochondrium, prominent blue veins in the neck, dark and purple complexion, cyanotic lips and nails, and edema of the lower extremities combined with a purple tongue, knotted/intermittent/uneven pulses.

*Guanxinshutong* (GXST) capsules have been developed by Shaanxi Buchang Pharmaceutical Co., Ltd. (Shaanxi, China) and gained approval by the China Food and Drug Administration (CFDA) for CHD treatment (approval number: Z20020055) in 2002. GXST consists of five herbal medicines (Table 1), and promotes blood circulation, removes blood stasis, and relieves pain (Zhang et al., 2016). Experimental studies have shown that GXST can inhibit ventricular remodeling through increasing mitochondrial productivity (Zhang et al., 2015; Zhang et al., 2016), repressing the expression of matrix metalloprotein-9, angiotensin receptors-1 and extracellular regulated protein kinases-2 (Zhang et al., 2012; Zhang et al., 2013), and the transforming growth factor-β/Smad signaling pathway (Fang et al., 2019) in myocardial tissue to improve CHF. A clinical trial with 61 patients reported that, compared with conventional treatment, combination with GXST could significantly increase left ventricular ejection fraction (LVEF) and cardiac output, and reduce the end-systolic, diastolic volume in patients with acute myocardial infarction with CHF (Li, 2019). Meanwhile, in our previous clinical study, GXST exerted a therapeutic effect on CHF (unpublished data), which implied that it might be a potential Chinese-patent medicine for CHF treatment. However, the current clinical data of GXST as a complementary therapy in CHF are lack of high quality, and limited in terms of methodology and sample size. Therefore, we designed a large-scale, multicenter, double-blinded clinical trial to investigate the efficacy and safety of GXST in CHF patients with reduced LVEF. The primary hypothesis of this study is as follows: combined with routine standard treatment, GXST is superior to placebo in patients with reduced LVEF caused by CHD.

**TABLE 1 T1:** Components of GXST (intervention drug).

Scientific name	Chinese Pinyin	Latin scientific name	Parts & form used
*Choerospondias axillaris* (Roxb.) B. L. Burtt & A.W. Hill.	Guang Zao	*Choerospondiatis Fructus*	Dried ripe fruit
*Salvia miltiorrhiza* Bunge	Dan Shen	*Salvia miltiorrhiza Bunge*	Dried root and rhizome
*Syzygium aromaticum* (L.) Merr. & L. M. Perry.	Ding Xiang	*Caryophylli Flos*	Dried flower bud
*Cinnamomum camphora* (L.) J. Presl.	Bing Pian	*Borneolum Syntheticum*	Essential oil
Bambusa textilis McClure	Tian Zhu Huang	*Concretio Silicea Bambusae*	Dried mass of secretion

## Methods and Analyses

### Design and Settings

This study is a multicenter, prospective, randomized, double-blind, placebo-controlled, superiority trial. The trial will be conducted by 11 centers throughout China (Table 2), and a total of 480 participants will be recruited. After the participants have been enrolled and provided written informed consent, they will be assigned randomly to the GXST group or placebo group in a 2:1 ratio. This trial consists of a 1-week baseline period, a 12-week intervention period, and a 40-week follow-up period. A flow diagram of the study procedures is illustrated in Figure 1. Participants will be monitored and assessed by the investigators at each study visit. The design follows the rules for Standard Protocol Items Recommendations for Interventional Trials (Chan et al., 2013) and Consolidated Standards of Reporting Trials (CONSORT) (Schulz et al., 2010).

**TABLE 2 T2:** Research setting.

Second Affiliated Hospital of Zhejiang Chinese Medical University
The Affiliated Hospital of Hangzhou Normal University
Pingdingshan First People’s Hospital
Hangzhou First People's Hospital
Fenyang Hospital of Shanxi Province
The Affiliated Hospital of Liaoning University of Traditional Chinese Medicine
Tongxiang Traditional Chinese Medicine Hospital
Shaoxing People's Hospital
Pizhou Traditional Chinese Medicine Hospital
Lishui Central Hospital
First Affiliated Hospital of Xinxiang Medical University

**FIGURE 1 F1:**
[figure not shown]
Flowchart of the clinical trial design. The template is from the CONSORT 2010 flowchart. GXST, Guanxinshutong; ACEI, angiotensin-converting enzyme inhibitor; AEs, adverse events; FAS, full analysis set; PPS, per protocol analysis set; SAS, safety assessment set.

### Recruitment

Recruitment strategies will include publishing recruitment advertisements on social media (e.g., QQ™, and We Chat™ in China, which are similar to Facebook™), online publications, and community centers. Patients who consent to participate will be examined and diagnosed by associate chief physicians to confirm their inclusion and will be registered on an online allocation system after written informed consent has been obtained.

### Study Population

The inclusion criteria and exclusion criteria are shown in Tables 3 and 4, respectively.

**TABLE 3 T3:** Inclusion criteria.

Meet all the diagnosis of CHD (Chinese Society of Cardiology and Chinese Medical Doctor Association, 2018), CHF (Ponikowski et al., 2016; Heart Failure Group of Chinese Society of Cardiology and Editorial Board of Chinese Journal of Cardiology, 2018), and TCM diagnosis of blood stasis syndrome according to the *Guidelines for Clinical Research of New TCM Drugs* (Zheng, 2002)
Aged 40–80 years, of both sexes
New York Heart Association class II–III (Hunt et al., 2005)
Left ventricular ejection fraction <50% (using two-dimensional echocardiographic Simpson's method)
Clinical findings of CHF for ≥3 months before screening
Clinically stable in the last 1 month or receiving standardized treatment for ≥1 month, and no modification of dosage or intravenous administration has been given. Standardized treatment includes ACEIs and/or angiotensin receptor blockers, β-blockers, aldosterone receptor blockers, or diuretics
Plasma level of NT-proB-type natriuretic peptide ≥125 ng/L
Volunteer, understand, and provide written informed consent

**TABLE 4 T4:** Exclusion criteria.

Acute coronary syndrome within the past 1 month
Plan to have cardiac surgery during the trial
Patients with cardiogenic shock, acute myocarditis, uncontrollable malignant arrhythmia, hypertrophic obstructive cardiomyopathy, pulmonary embolism, or severe valvular disease necessitating surgery
Uncontrolled hypertension, systolic blood pressure (SBP) ≥180 mmHg, and/or diastolic blood pressure (DBP) >110 mmHg; or SBP <90 mmHg and/or DBP <50 mmHg
Combined with severe liver or kidney dysfunction or active liver disease, and/or aspartate transaminase, alanine aminotransferase ≥3 times the upper limit of normal
Patients with diseases affecting walking ability, such as vascular disease of lower extremities
Combined with psychiatric manifestations
Patients with alcohol addiction or history of substance abuse
Females who are pregnant or lactating, preparing for pregnancy during the trial, or have a positive pregnancy test at the time of hospital admission
Have severe allergies, or allergic to research drugs and its ingredients
Patients with a history of previous or present malignancy, or precancerous lesions confirmed by pathology
Participation in other clinical studies within 3 months
Researchers estimate that the patient unable to complete the study

### Criteria for Withdrawal, Removal, Dropout, and Termination

The withdrawal criteria will be 1) exacerbation or deterioration that is clearly related to intake of the study drug; 2) an allergic reaction that is clearly associated with the study drug; 3) comorbidities, complications, adverse events (AEs), or serious adverse events (SAEs) during the trial, such as the necessity of long-term intravenous medication, repeated hospitalization for heart failure, or New York Heart Association (NYHA) class-IV symptoms; 4) the use of forbidden drugs or receipt of prohibited treatment affect the measures of efficacy and safety; 5) poor compliance by participants, or the amount of drug used does not meet the regulations (<80% or >120%); 6) participants request to withdraw from the study; 7) the blinding is uncovered or emergency unblinding is required.

Participants who fail to complete the observational period proposed in the trial, regardless of time and reasons, will be considered to be “dropout” cases. Reasons for dropout will be recorded in electronic case report forms (eCRFs), and the last data recorded will be included in data analyses. During the trial, a participant may be removed if he/she 1) is included mistakenly due to a misdiagnosis, 2) has not taken medication after study inclusion, 3) is participating in other clinical trials, and 4) has incomplete data and no evaluable records after inclusion. Another reason for removal is if the combined use of drugs has a great influence on the efficacy and safety of the study drug. Removal cases will not be included in analyses of the intention-to-treat (ITT) population.

The entire research study will be terminated if 1) there is a poor clinical effect of the test drug, and there is no need to continue the trial; 2) there are major defects in the trial; and 3) administrative authorities terminate the trial.

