### Statistical Analyses

The statistical analysis plan will be specified before data analyses. The statistical analyses will be undertaken *via* Statistical Analysis System v9.4 (or higher version) by the Department of Medical Statistics, Peking University First Hospital. Professional statisticians who are independent of all other processes of our study will carry out analyses. Consistent with the CONSORT statement and ITT principle, and the last observation, carried forward method will be used for missing values. Cases in the per protocol set (PPS) will be those who adhere to the protocol closely without the absence of baseline characteristics. Analyses of primary outcome and curative effect will be carried out using a full-analysis-set approach and PPS approach. The safety analysis set will include all randomized patients who have accomplished at least one study visit. Participating centers will be required to sum-up participant numbers in each center and list participants who have been removed from PPS.

For continuous variables, we will calculate the mean, SD, median, minimum, maximum, and interquartile range. For categorical variables, we will describe various frequencies or percentages. The chi-square test or Fisher's exact test will be used for categorical variables. The Student's *t*-test will be used for continuous variables with a normal distribution. For data that do not have a normal distribution, intragroup or intergroup differences before and after treatment will be analyzed by the Wilcoxon rank-sum test. The proportion of patients with AEs in two groups will be compared using the chi-square test or Fisher's exact test. Because patients who had use of ARNIs before the recruitment may constitute a specific population, we will run sensitivity analyses of the outcomes with patients used ARNIs as basic treatment, and adjusted for the effect of ARNIs. Significance will be assumed at a two-sided *p*-value less than 5%. The relative risk with corresponding 95% confidence interval to compare dichotomous variables will be calculated. Table 6 shows the method of analysis for specific outcomes.

**TABLE 6 T6:** Outcomes and methods of analyses.

Outcome/variable	Hypothesis	Measures	Methods of analyses
Baseline balance test			
		Quantitative outcomes (age, temperature, heart rate, respiratory rate, and blood pressure)	*t*-test/Wilcoxon rank-sum test

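### The ITT population drops participants removed for concomitant drug use during the trial, which contradicts the stated ITT principle and overlaps with rules that keep such participants

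*Protocol article*

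**What the plan says.** The section Criteria for Withdrawal, Removal, Dropout, and Termination sets out three labels.

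- **Withdrawal.** Criterion 4 is "the use of forbidden drugs or receipt of prohibited treatment affect the measures of efficacy and safety". Criterion 3 covers adverse events and deterioration, such as repeated heart-failure admission or NYHA class IV symptoms.
- **Dropout.** This is anyone who does not complete the observation period, whatever the time or reason. For them, "the last data recorded will be included in data analyses".
- **Removal.** The list opens "During the trial, a participant may be removed if he/she 1) is included mistakenly due to a misdiagnosis, 2) has not taken medication after study" (that is, after entry). It goes on to participation in other trials, and to incomplete data combined with no evaluable records. A further ground follows: "Another reason for removal is if the combined use of drugs has a great influence on the efficacy and safety of the study drug". The consequence is that "Removal cases will not be included in analyses of the intention-to-treat (ITT) population".

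The Interventions section adds a fourth label. Participants who deteriorate so far that continuing is inadvisable are classed in the analysis as treatment ineffective.

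Statistical Analyses says: "Consistent with the CONSORT statement and ITT principle, and the last observation, carried forward method will be used for missing values". It also says: "Analyses of primary outcome and curative effect will be carried out using a full-analysis-set approach and PPS approach". The article does not define the FAS, and nothing in it returns removed participants to an efficacy analysis.

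**The concern.** An ITT population is fixed by randomisation. A rule that takes randomised participants out because of drugs used during the trial cannot be squared with the ITT principle that the same article claims.

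The co-medication ground is the clear fault. It is applied during the trial and is discretionary. It has no drug list or threshold, and no adjudication blind to arm is described. Interventions itself links added treatment to acute exacerbation, so drug use can be a consequence of how the patient responds. If response differs by arm, removal can differ by arm too, and the participants left no longer form the randomised comparison.

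The labels also overlap. A patient given additional drugs could reasonably be filed under any of them, and the choice decides whether that patient's data count. The 6-minute walk distance (6MWD) comparison is at stake, provided the FAS inherits the exclusion.

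**Working it through.** **1. The plan's own figures.** Sample Size uses a 30 m effect, SD 100 m, α = 0.025 (read as one-sided), 80% power and 2:1 allocation. The plan's formula gives (1.96 + 0.84)² × (100/30)² × 1.5 ≈ 130.8 for placebo and twice that for GXST, 392.4 in total. Then 392.4 × 1.2 = 470.9, which matches the stated 470 (rounded up by the plan to 480: 320 + 160). The point below does not depend on this total. It uses only the 30 m, the 100 m and the arm sizes.

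**2. The rules side by side.** Take a participant who starts an additional, influential drug in week 6.

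| Rule | Where | Consequence |
|---|---|---|
| Withdrawal criterion 4 | Criteria section | Leaves the study; as a non-completer, also meets the dropout definition |
| Dropout | Criteria section | Last recorded data analysed |
| Treatment ineffective (if deteriorating) | Interventions | Classed as a failure in the analysis |
| Removal for co-medication | Criteria section | Out of the ITT population |

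No stated rule separates the first and last rows, and a participant removed mid-trial also fits the second.

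**3. Size of the possible bias.** The protocol gives no removal rates and no outcome for removed patients, so these inputs are assumptions. Let r be the share removed in each arm, and D the amount by which the removed patients' 6MWD change falls short of that of those kept, equal in both arms. The arm mean is (1 − r) × K + r × (K − D) = K − rD, where K is the mean of those kept. Dropping the removed patients therefore raises the arm mean by rD, and the GXST-minus-placebo difference shifts by

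(r_GXST − r_placebo) × D.

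Type I error below assumes no true effect, SD 100 m and the remaining participants analysed, with SE = 100 × √(1/n_placebo + 1/n_GXST).

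| Removed placebo / GXST | Shift, D = 50 m | Shift, D = 100 m | SE | Two-sided type I error |
|---|---|---|---|---|
| 5% / 5% | 0 | 0 | 9.93 | 5.0% |
| 10% / 5% | −2.5 m | −5.0 m | 10.12 | 5.7% to 7.8% |
| 5% / 10% | +2.5 m | +5.0 m | 10.03 | 5.7% to 7.9% |
| 15% / 5% | −5.0 m | −10.0 m | 10.32 | 7.7% to 16.3% |

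Against 30 m, a shift of 2.5 to 5 m is 8% to 17%.

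**4. Whether re-inclusion alone repairs it.** 6MWD is scheduled only at baseline and week 12 (Table 5). Last observation carried forward (LOCF) therefore enters a missing week-12 value as zero change. As an example, assume true mean changes of +20 m (placebo) and +50 m (GXST), with removed patients in both arms at −60 m.

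- **10% placebo / 5% GXST removed.** Exclusion gives (50 + 3)/0.95 − (20 + 6)/0.90 = 55.79 − 28.89 = 26.9 m. Re-inclusion at zero change gives 0.95 × 55.79 − 0.90 × 28.89 = 53.0 − 26.0 = 27.0 m.
- **5% placebo / 10% GXST removed.** Exclusion gives (50 + 6)/0.90 − (20 + 3)/0.95 = 62.22 − 24.21 = 38.0 m. Re-inclusion at zero change gives 56.0 − 23.0 = 33.0 m.

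The true difference is 30 m in both. Re-inclusion with LOCF corrects almost nothing in the first case and only part in the second. The week-12 measurement itself is needed.

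**The case against.** Four points can fairly be made for the plan.

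- **Not every removal ground is a post-randomisation event.** A reader might infer that the whole list is. The text does not support that. Misdiagnosis is a fact that predates randomisation. Participation in another trial may simply restate the exclusion criterion in Table 4. The last numbered ground requires incomplete data and also no evaluable records. Exclusions of never-dosed or record-free participants are common and carry less risk when judged blind. This stands, and it narrows the point to co-medication.
- **Many deteriorating patients are directed elsewhere.** Withdrawal criterion 3, the dropout rule and the treatment-ineffective class all point away from deletion, and Interventions asks for stable concomitant doses. This also stands, so removal does not necessarily track the outcome. It does not settle which label prevails when several apply.
- **The primary outcome is assigned to the FAS, not to an ITT population.** The article never equates the two, and neither Figure 1 nor the statistical analysis plan is available. It would be too strong to state as fact that the main analysis abandons the randomised comparison.
- **The trial is double-blind.** Blinding makes differential removal less likely. It does not exclude it, because response can drive added drug use without anyone knowing the arm, and emergency unblinding is allowed.

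The contradiction itself survives: the article fixes the exclusion rule in its current text, so it has not been left to the analysis plan.

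**Conclusion.** The point holds in a limited form. Excluding participants from the ITT population because of concomitant drug use during the trial contradicts the ITT principle stated in the same article. The removal, withdrawal, dropout and treatment-ineffective rules overlap without an order of precedence.

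That this can bias the 6MWD comparison rests on the FAS following the removal rule, which is an inference. Neither size nor direction can be derived from the document. The 2.5 to 5 m for a 5-point imbalance assumes a common deficit of 50 to 100 m; under that model balanced removal produces no shift. A reader might take a single larger figure, such as the 38.0 m in the example, as the expected distortion. The documents do not support that, because it depends on one assumed outcome for removed patients and a twofold imbalance between arms.

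**What to change.** Before unblinding, by amendment or in the analysis plan:

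- Define the ITT/FAS as all randomised participants, analysed as allocated.
- Limit any exclusion to prespecified reasons judged blind to arm, such as ineligibility shown by facts that predate randomisation.
- Let concomitant drug use lead to exclusion from the per-protocol set only.
- Reconcile the removal, withdrawal and dropout rules with the treatment-ineffective class in Interventions, so that each event has one stated consequence for the analysis.
- Collect the already scheduled week-12 6MWD in removed or withdrawn participants where possible. Without it, LOCF imputes zero change and re-inclusion repairs little.

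The cost is wording, plus some added follow-up of participants who stop treatment. No extra patients are needed. The estimate may move in either direction.
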